### Intervention

The intervention applied to the CG will be brief advice, which will be serious, firm, concise, personalised and appropriate for the phase of change. The brief advice attempts to encourage subjects in a clear, firm and personalised way to quit smoking, inform more than oblige, facilitate information on the negative effects of tobacco on health, highlight the main advantages of quitting smoking and ask them to identify and examine the main obstacles when quitting smoking. Once the brief advice to stop smoking has been carried out verbally, the patients will be given a written document with advice and several guidelines. The healthcare professionals will receive training on how to give the brief advice.

In the IG, apart from giving the brief advice in exactly the same way as for the CG, a CO-oximetry test will also be carried out on each subject. Before it is performed, the basics of the test and what it measures will be explained to patients. Once the subject has properly understood how the technique works and if he/she is at an optimum moment for it to be carried out (having not smoked one hour prior to the test/having not smoked for more than 10 hours), the levels of carbon monoxide in expired air will be measured in parts per million (ppm) and recorded in the data collection booklet (DCB) and in a personal report that will be given out to the subject, together with an explanation and definition of CO-oximetry and an interpretation of the possible results.

The two interventions will be carried out by the healthcare professional including the patient in the trial, irrespective of whether he/she is a GP or a nurse. It will only be performed once, during the first visit following the inclusion of the patient into the study. Each professional will conduct one intervention or the other, depending on what intervention is assigned to the subject during randomisation.

The evaluation at months 6 and 12 will be done by a nurse blinded to patient allocation. At 6 months there will be a telephone evaluation and at 12 months an evaluation in the primary health centre.

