The majority of non-pharmacological interventions for smoking cessation use the so-called transtheoretical model of change described by Prochaska and DiClemente at the beginning of the 90s [9]. According to this model, the smoker goes through a series of phases during his/her smoking cessation process: pre-contemplative (the smoker does not contemplate quitting smoking), contemplative (the smoker begins to be unhappy with his/her addiction and starts thinking about quitting smoking within the next 6 months), preparative (the smoker is prepared to quit smoking), smoking cessation and the eventual relapses that re-start the cycle.

The brief advice given by a healthcare professional can achieve between 1–3% smoking cessations after 6 months, taking into consideration that an additional 2–3% manage to quit smoking without help. Therefore, this measure is moderately effective, although it has a great impact across the population [10] and the percentage can be increased if the advice is not as brief and/or if it is accompanied by self-help and/or follow-up materials [11]. In order to increase the rates of smoking cessation by means of brief advice, another strategy could be the evaluation of the physical effects of smoking using physiological measures that offer the smoker some feedback on the effects of smoking, as happens with hypertensive patients and blood pressure readings [12].

These interventions are based on the hypothesis that one of the reasons why people continue smoking, in spite of knowing the harmful effects of tobacco, is that they underestimate the personal risk of becoming ill because of it. In this sense, the interventions will offer motivational feedback to promote awareness of the risk [13]. It has been suggested that some smokers who manage to quit smoking are more aware of the adverse effects of tobacco or to have had their health seriously compromised [14,15].

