### Recruitment of subjects

Every person consulting a general practitioner (GP) or a nurse will be asked about their smoking behaviour and their attitude toward quitting smoking. To establish the patient’s phase or period of change, he/she will be asked the following: “have you ever seriously thought that you should quit smoking within 1 month?”, following the model of question used in the ISTAPS project [24].

If the subject fulfils the inclusion criteria, information on the study will be released, the subject invited to participate and, upon acceptance, will provide signed informed consent. Subsequently, the participant will be randomised to either CG or IG.

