### Study development

*a).* A pilot study will be carried out in two health centres to proceed with the creation of the final DCB based on comments and suggestions from the GP and nurse participants. *b).* Training will be given to the professional participants in the study regarding brief advice and how to carry out the CO-oximetries to ensure that data collection is as homogeneous as possible. The nursing staff contracted for the development of the evaluations will also receive this training. *c).* A total of 3 contacts with each subject will be carried out. The first contact: inclusion-intervention visit will be carried out by the health centre’s professional participants. Two assessment contacts: a 6 month phone assessment and a final assessment at 12 months in the health centre will be performed by the nursing staff contracted for the study who will not have any knowledge of the randomisation scheme. *d).* On the first visit, once the subject has signed the informed consent and been randomised, baseline information will be collected by means of the basal DCB (socio-demographic variables, smoking habits variables, and other variables related to the consumption of drugs, diseases and cardiovascular risk factors). Subsequently, the intervention will be carried out. *e).* Six months after inclusion, the independent and dependent measurements mentioned above will be collected by means of another DCB by phone. *f).* the final assessment will be carried out at 12 months. The DCB will contain the same questions as those administered at 6 months, the urine cotinine test will be used to confirm sustained smoking cessation in those claiming to have quit smoking, and a CO-oximetry will be performed on patients in both groups. g). If a subject requests help to quit smoking during the study, he/she will be aided and referred to his/her GP or nurse to proceed with the intervention. This information will also be recorded.

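### The first visit reveals the allocation before the brief advice is given, which leaves an avoidable route for performance bias in the CO-oximetry comparison

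*Protocol article*

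**What the plan says.** All references are to the protocol article.

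- **Same advice in both arms.** Intervention: "In the IG, apart from giving the brief advice in exactly the same way as for the CG, a CO-oximetry test will also be carried". The advice is verbal, personalised and adapted to the phase of change, and is followed by a written document. Professionals are trained to give it.
- **Order of the visit.** Recruitment of subjects, after consent: "Subsequently, the participant will be randomised to either CG or IG". Study development, item d: "once the subject has signed the informed consent and been randomised, baseline information will be collected by means of the basal DCB", and then "Subsequently, the intervention will be carried out".
- **Who delivers.** Intervention: "The two interventions will be carried out by the healthcare professional including the patient in the trial". The same section adds: "Each professional will conduct one intervention or the other, depending on what intervention is assigned to the subject during randomisation".
- **Concealment and blinding.** Random allocation to study arms provides sequentially numbered, closed, opaque envelopes, 20 per professional. Intervention and Study development (item c) blind only the nurse who assesses at months 6 and 12.
- **Effect of the advice.** Background credits brief advice with 1–3% cessation after 6 months and adds that "the percentage can be increased if the advice is not as brief and/or if it is accompanied by self-help and/or follow-up materials".

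**The concern.** The contrast of interest is advice plus CO-oximetry against advice alone. It measures the CO component only to the extent that the advice is alike in both arms. Under the stated order, the person giving the advice already knows whether a CO test will follow. That knowledge could lead a professional to be more emphatic when the test is coming, to shorten the advice when it is not, or to give controls more in compensation. Any such difference would be part of the between-arm contrast, and the direction cannot be predicted.

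Randomisation does not protect against this, because the difference would arise after assignment. The blinded follow-up nurse and the cotinine confirmation protect the measurement of the outcome, not the delivery of the advice. The same order also means that baseline data, including phase of change, are recorded by someone who knows the arm. Change of phase is a secondary outcome.

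**Working it through.** **Step 1. The sequence.** Put side by side, the sections give:

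| Step | Source | Arm already assigned? |
|---|---|---|
| Consent | Recruitment of subjects | No |
| Randomisation | Recruitment of subjects | Assigned here |
| Baseline booklet | Study development, d | Yes |
| Advice, or advice plus CO-oximetry | Study development, d; Intervention | Yes |

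The article does not name the moment at which the envelope is opened. With randomisation placed before baseline data and intervention, and the professional acting on the assignment, there is little room for another reading.

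**Step 2. What each safeguard covers.**

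- Opaque envelopes: the assignment, not what follows it.
- Blinded nurse and cotinine test: the outcome.
- Training: teaches the advice but does not hide the arm.
- Written document: standardises the written part only.
- Individual randomisation within each professional: spreads differences between professionals over both arms, but not differences that one professional makes by arm.

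**Step 3. The plan's own figure.** Inputs from Sample size: 5% in the control group, a 5-point difference (so 10%), two-sided alpha 0.05, power 80%, 10% loss. The arcsine formula gives n = 2 × [(1.960 + 0.842) / h]², with h = 2·arcsin√0.10 − 2·arcsin√0.05 = 0.1925. Then n = 424 per arm, and 424 / 0.90 = 471.1. The stated 471 per group reproduces. Nothing in this point changes it.

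**Step 4. Scale, on assumed values.** The documents give no size for an arm difference in advice. If it were worth 1 or 2 points, it would be 1/5 = 20% or 2/5 = 40% of the target difference.

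To see what that would do, take 471 per arm, 5% in controls and a two-sided 5% test of two proportions. Let d be the difference actually present between the arms, p̄ the mean of the two rates, SE₀ = √[2p̄(1−p̄)/471] and SE₁ = √{[p₁(1−p₁) + p₂(1−p₂)]/471}. The chance of a significant result favouring the intervention group is Φ[(d − 1.96·SE₀)/SE₁]. For d = 0.02, SE₀ = 0.01548 and SE₁ = 0.01546, so the chance is Φ(−0.67) = 25%.

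*CO-oximetry has no effect; the advice favours the intervention group by d:*

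| d (points) | Chance of a significant result for the intervention group |
|---|---|
| 0 | 2.5% |
| 0.5 | 5% |
| 1 | 10% |
| 2 | 25% |
| 3 | 46% |

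Three points is an extreme case, because it equals the top of the range that Background gives for brief advice as a whole.

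*CO-oximetry is worth 5 points; the advice favours controls:* if the contrast shrinks from 5 points to 4 or 3, the same formula gives power of 83%, 67% and 46%.

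**The case against.** The strongest case against is that this is neither an error nor a contradiction. The trial is declared single-blind, a provider cannot be blinded to a feedback test, and randomising before the assigned intervention is the usual order. The plan lists the content of the advice, trains the professionals, hands out a written document and randomises patients individually within professionals. A reader might infer that the trial *cannot* isolate the effect of CO-oximetry. The documents do not support that: they show that the advice could differ by arm, not that it will. A reader might also fault the lack of a script or fidelity check, but a journal article commonly leaves such detail to the full protocol or the training material, so that is not part of the point.

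The objection to the size also stands. The 1–3% in Background is the 6-month effect of brief advice itself, not the effect of varying its intensity between arms. The primary outcome is sustained cessation at 12 months, for which that section gives no figure for advice.

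Two practical objections bear on the fix:

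- Moving the advice forward without saying where the baseline booklet goes could let the advice alter the recorded baseline phase, or move a patient into the excluded preparation phase before allocation. This stands, and the fix deals with it.
- The Discussion relies on brief advice to offset falsely reassuring normal readings, so advice after the reading may be intended. This does not defeat the fix: advice adapted to a reading would not be the same advice that controls receive. Interpretation of the result already has a place in the personal report.

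What remains is that the order is stated, not omitted. It exposes the advice to knowledge of the arm without need.

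**Conclusion.** The point holds as an avoidable risk of performance bias. As written, an unblinded professional knows the arm before giving personalised advice that is meant to be identical, and before collecting baseline data. The stated safeguards reduce the risk in part. Its direction is unknown and its size cannot be derived from the documents; the 20–40% share and the error rates above rest on assumed differences in advice. The conclusion also assumes that randomisation means the professional learns the arm at that moment, which is the natural reading. This is a cheap improvement worth making. It does not show that the primary comparison is invalid, and the sample size is not affected.

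**What to change.** Reorder the first visit in Recruitment of subjects, Intervention and Study development (item d):

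1. Consent and the eligibility/phase check.
2. Baseline data collection booklet.
3. Verbal brief advice and the written document, for every patient.
4. Opening of the next sequential envelope.
5. Control patients finish the visit. Intervention patients go on to the CO explanation, the test and the personal report with its interpretation.

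State that eligibility and baseline phase are fixed before the advice and are not reassessed after it.

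The cost is a change to the text and the training; staff, visits, procedures and sample size stay the same. There are two small downsides. In the intervention group the advice comes before the CO reading, so discussion of the reading belongs to the CO component. A patient who leaves after the advice but before the envelope is opened is not randomised.

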### Outcome assessment

#### Primary outcome measure

Sustained smoking cessation at 12 months confirmed by a urine cotinine test. It will be considered successful if the values are below 100 ng/ml.

#### Secondary outcome measures

Point smoking cessation at month 6 and/or month 12 confirmed by a urine cotinine test; self-declared smoking cessation at months 6 and 12; reduction in the number of self-declared cigarettes consumed when smoking cessation is not accomplished at months 6 and 12; variation in the phase of process of smoking cessation: from pre-contemplation to contemplation or preparation phase, or from contemplation to preparation phase, at months 6 and 12.

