### Sample size

Accepting an alpha risk of 0.05 and a beta risk of 0.20 in a bilateral contrast, and estimating a rate of loss to follow-up of 10%, 471 subjects in both the control group (CG) and the intervention group (IG) are required in order to detect a difference equal or superior to 5% between groups. A proportion of 5% smoking cessation is estimated in the CG. In total, a sample size of 942 subjects is required.

Forty-eight health care professionals from 16 health care centres will participate in the study. It is expected that each professional will include approximately 20 subjects to attain the sample size required.

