#### Independent measures

Type of intervention: brief advice or brief advice together with CO-oximetry. At baseline, the following information will be obtained: (a) socio-demographic variables: gender, age, social class measured by means of two indicators suggested by the Spanish Society of Epidemiology: educational level and occupation; (b) regarding the patient’s smoking behaviour: number of cigarettes/day and number of years the patient has been smoking (the number of packets/year will be calculated based on this information); concentration of nicotine and tar smoked currently (obtained from the type of tobacco consumed); number of times the patient has tried to quit smoking and reasons for relapse; maximum amount of time without smoking; tobacco consumption during work, with family and/or friends; physical dependency on nicotine using a simplified version of the Fagerström test; phase of the smoking cessation process: Prochaska and DiClemente phases (pre-contemplation, contemplation, preparation, cessation and relapse); any intervention to quit smoking during the past year; (c) other measures: consumption of other legal drugs (alcohol, psychopharmacological drugs); consumption of illegal drugs (cannabis, cocaine and others); basal disease associated with tobacco consumption (Chronic Obstructive Lung Disease, cancer, ischemic myocardiopathy, cerebrovascular disease); other cardiovascular risk factors (HTA, diabetes mellitus, dyslipidaemia, obesity); mental illness.

At months 6 and 12 the following data will be collected: Smoking behaviour/status (does the patient smoke or has he/she quit); date of smoking cessation, whether the patient has quit smoking; time interval without smoking between date of intervention till six month assessment; participation in a programme for smoking cessation since the beginning of the study.

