### Statistical analysis

The statistical analyses will be carried out using the SPSS programme for Windows v 12.

Descriptive, labelled analyses and data refinement: evaluation of the atypical and extreme values (“outliers”), detection and labelling of the lost and/or not applicable values. We will perform descriptive analysis, with continuous variables summarised by their means and standard deviations for normal distributions, and by median and 25th and 75th percentiles for non-normal distributions.

Basal comparative analysis: Comparison of socio-demographic characteristics, smoking behaviour and other variables collected by means of the t Student and chi-squared tests. If normality is not met, non-parametric tests will be applied.

Final comparative analysis: Comparison of the dependent variables in both groups by means of the t Student and the chi-squared tests. If normality is not met, non-parametric tests will be applied. The relevance of the intervention will be determined from the percentage of patients with sustained smoking cessation in both groups - the relative risk (RR), the reduction in relative risk (RRR), the reduction in absolute risk (RAR), and the number of intent to treat patients (ITT) necessary will be calculated. All the analyses will be carried out based on intent to treat. The patients lost to follow-up will be considered as smokers. The level of statistical significance is established at 5% (bilateral).

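### Cigarette reduction is defined only in participants who have not quit, and phase change lists no move to cessation, so the arm comparison on these two secondary outcomes can be biased and gives no credit for quitting

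*Protocol article*

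**What the plan says.** All references are to the Protocol article.

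- **Secondary outcome measures**, cigarettes: "reduction in the number of self-declared cigarettes consumed when smoking cessation is not accomplished at months 6 and 12".
- **Secondary outcome measures**, phase variation: "from pre-contemplation to contemplation or preparation phase, or from contemplation to preparation phase, at months 6 and 12". These are three moves, and preparation is the furthest end point.
- **Independent measures** lists the phases of the same process as "pre-contemplation, contemplation, preparation, cessation and relapse", so cessation is one of the protocol's own phases.
- **Statistical analysis**: "All the analyses will be carried out based on intent to treat". The section compares the dependent variables between the two groups with t and chi-squared tests, or non-parametric tests where normality fails. It counts participants lost to follow-up as smokers and gives them no value for cigarettes/day or phase.
- **Background**, last paragraph: the aims of reducing cigarettes and changing motivation are stated for smokers in the two eligible phases, with no restriction to those who go on smoking.

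**The concern.** If the intervention raises quitting, it takes more people out of the cigarette comparison in the intervention group (IG) than in the control group (CG). The two sets left are no longer comparable by randomisation, although the plan tests them as arm comparisons and does not call them descriptive.

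A participant who goes from contemplation to cessation has made the largest advance on the scale and still fits no listed move. That person is either excluded, which raises the same problem, or counted as not having progressed, which keeps everyone in the denominator but scores the best result as none. The article does not say which applies.

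The interpretation of two outcomes named in the trial's aims is at stake. The main efficacy conclusion is not.

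**Working it through.** **Planning figures.** Sample size gives "Accepting an alpha risk of 0.05 and a beta risk of 0.20 in a bilateral contrast", "A proportion of 5% smoking cessation is estimated in the CG", and the aim to "detect a difference equal or superior to 5% between groups", hence 10% in IG. It also assumes 10% loss and arrives at 471 per group.

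The 471 reproduces with the arcsine formula:
- h = 2·asin(√0.10) − 2·asin(√0.05)
- n = 2·((1.960 + 0.842)/h)² = 423.7
- 423.7/0.90 = 470.8, rounded up to 471

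The planning rates can therefore be used as they stand.

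**Size of the excluded set.** CG: 0.05 × 471 ≈ 24. IG: 0.10 × 471 ≈ 47.

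**Cigarettes.** Assume that 5% of participants would quit in either arm, 5% only under IG, and 90% in neither. Those who quit in neither arm cut r = 2 cigarettes/day in both arms, so there is no true effect among them. The extra 5% would have cut R in CG. Baseline is B = 20/day. The article gives none of r, R or B.

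- Non-quitters: CG mean = (0.05R + 0.90r)/0.95; IG mean = r = 2.00.
- All randomised, quitters at 0: CG = 0.05B + 0.05R + 0.90r; IG = 0.10B + 0.90r = 3.80.

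| R | CG non-quitters | IG − CG, non-quitters | CG, all randomised | IG − CG, all randomised |
|---|---|---|---|---|
| 10 | 2.42 | −0.42 | 3.30 | +0.50 |
| 6 | 2.21 | −0.21 | 3.10 | +0.70 |
| 2 | 2.00 | 0.00 | 2.90 | +0.90 |
| 0 | 1.89 | +0.11 | 2.80 | +1.00 |

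The last column equals 0.05(B − R). With B = 15 it runs from +0.25 (R = 10) to +0.75 (R = 0). The non-quitter contrast does not depend on B. Its sign depends only on whether R is above or below r.

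**Phase, three assumed cases.**

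1. The extra quitters would otherwise have moved forward, and 20% to 40% advance in total (quitters included).
   - Scored as not moved: 15% v 10%, up to 35% v 30%, so −5 points.
   - Excluded: 15/95 v 10/90 = −4.7 points; 35/95 v 30/90 = −3.5 points.
   - Cessation counted as forward: equal in both arms, so 0.
2. Quitters are a random subset, with f = 10% to 50% of non-quitters moving forward in both arms.
   - Scored as not moved: −0.05f = −0.5 to −2.5 points.
   - Excluded: 0.
   - Cessation counted as forward: 0.05(1 − f) = +4.5 to +2.5 points.
3. The extra quitters would otherwise have stayed put, with g = 10% to 50% of the remaining 90% moving forward.
   - Scored as not moved: 0.90g in both arms, so 0.
   - Excluded: g − 0.90g/0.95 = +0.5 to +2.6 points.
   - Cessation counted as forward: +5 points.

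**The case against.** The best defence is that cessation has its own outcomes (primary, point and self-declared), and that reduction and phase are meant to describe people still smoking. That is a recognisable design choice and the figures are useful. A journal article may also leave the scoring of quitters on a secondary outcome to the full protocol.

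Part of this stands. Quitters are not lost to the trial, and the phase half is partly an ambiguity: the article does not state that quitters are mis-scored. If they are kept and scored as not moved, the comparison is still a randomised one with a poor scoring rule. The direction of bias is not fixed either, as the table shows. A spurious deficit would also seldom be declared: with an assumed SD of 5 to 9 cigarettes/day and 424 per arm, power to detect a deficit of 0.3 to 0.42 is only 7% to 23%.

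The central point is not answered. The restriction to non-quitters is written into the definition, so it is not detail left for later, and it disagrees with the article's own analysis rule and objective. Counting quitters under another outcome does not restore comparability here.

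**Conclusion.** The point holds for these two secondary outcomes. Cigarette reduction is conditioned on a post-randomisation event that the treatment is meant to change, and the phase outcome has no place for a participant who quits.

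At the planned quit rates the distortion in cigarettes is about −0.4 to +0.1 per day. In phase it is about −5 to 0 points if quitters are scored as not moved, and about −4.7 to +2.6 points if they are excluded. All of these rest on assumed behaviour of the extra quitters, and the cigarette figures also on an assumed cut of 2/day in continuing smokers.

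A reader might infer that an effective intervention would look null or harmful. The documents do not support that. It would require the effect to act mainly through quitting, or the extra quitters to be people who would otherwise have cut down or advanced more than others. An effect among continuing smokers could still show, and efficacy is judged on cotinine-confirmed sustained cessation, which is untouched.

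**What to change.** 1. Compare the change in cigarettes/day at months 6 and 12 in all randomised participants, entering quitters as 0. State which cessation status triggers the zero.
2. Define phase progression as any forward move, including to cessation, in all randomised participants.
3. Score losses in line with the existing rule that they are smokers, for example no change from baseline in cigarettes/day and phase. At the planned 10% this is about 47 per arm, twice the 5-point difference in quitting, so it cannot be left open.
4. Report the non-quitter figures beside these as descriptive, without a between-arm test.

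The cost is a few changes of definition. Study development already has the dependent measures collected at both follow-ups, so no new data are needed. The downside is that the reduction outcome then includes the quitting effect and no longer isolates cutting down among continuing smokers; the descriptive figure is kept for that reason. Scoring losses as unchanged is itself an assumption and should be stated as one.

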Three different types of feedback have been established: the first type analyses biomarkers of exposure to tobacco (nicotine, carbon monoxide); the second offers information regarding the risk of tobacco-related diseases (predisposition to lung cancer according to the CYP2D6 genotype); and the third describes the harmful effects of smoking (atherosclerotic plaques or worsening of pulmonary function) [15]. Isolated studies have provided mixed results regarding the effect of biomedical risk assessment as an aid for smoking cessation. A recent systematic review [16] concludes that, due to the lack of good quality evidence, it is not possible to draw firm conclusions. The following methodological recommendations are made: use adequate sample sizes, use allocation concealment procedures, agree on a definition of “abstinence” and systematically introduce measures to biochemically confirm it and, finally, carry out analyses by intention to treat. The measurement of CO levels in exhaled air by CO-oximetry is used to evaluate the degree of smoking by the smoker given that, in general, there is a direct relationship between the levels of CO and the number of cigarettes smoked [17]. The measurement of exhaled CO is also the preferred measurement to confirm tobacco abstinence [18].

It has been observed that the measurement of CO in exhaled air in smokers could be an indicative test of immediate and future harm to their health as a consequence of smoking [19] and this could increase their motivation to stop smoking, which could lead to smoking cessation in these patients. In the review mentioned above [16], three studies that measured the direct effect of CO-oximetry on smoking cessation [20-22] were identified. Two of them were carried out in primary care settings [20,21]. No positive changes in the rate of smoking cessation were observed.

The measurement of CO levels in exhaled air by CO-oximetry is an inexpensive, non-invasive, fast technique that requires little technical training [23] making it a technique for risk assessment in smokers that can be easily applied in primary care and, if proven effective, could serve as a reinforcement aid in smoking cessation intervention activities.

Therefore, we think it would be interesting to study its possible effect on smoking cessation to a greater extent through the design of a new study incorporating the methodological recommendations given by the experts, and by providing more robust results to determine efficacy.

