## Methods/Design

### Design and settings

A randomised, parallel, single-blind clinical trial in a primary health care setting in Majorca (Spain). The subjects will be randomised to either Control Group (CG) or Intervention Group (IG). Participants in CG will receive brief advice; participants in IG will receive brief advice with CO-oximetry.

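### Cigarette reduction is judged on self-report alone, while the month-12 exhaled CO reading already taken in both arms is given no role

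*Protocol article*

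**What the plan says.** The last paragraph of the Background makes fewer cigarettes at month 12 one of the study's aims. Secondary outcome measures turns this into "reduction in the number of self-declared cigarettes consumed when smoking cessation is not accomplished at months 6 and 12".

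On verification, Study development (item f) says that "the urine cotinine test will be used to confirm sustained smoking cessation in those claiming to have quit smoking". The same item says that at the final visit "a CO-oximetry will be performed on patients in both groups". That month-12 CO reading does not appear under Primary outcome measure, Secondary outcome measures, the month-6 and month-12 data list in Independent measures, or Statistical analysis.

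On blinding, Design and settings calls the study "A randomised, parallel, single-blind clinical trial", and Intervention explains that "The evaluation at months 6 and 12 will be done by a nurse blinded to patient allocation". In the intervention group the test is explained beforehand and the result goes into "a personal report that will be given out to the subject, together with an explanation and definition of CO-oximetry". The control group has no CO test at baseline.

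On the value of CO, the Background states, as a general tendency, that "there is a direct relationship between the levels of CO and the number of cigarettes smoked".

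**The concern.** A blinded assessor protects a measurement that the assessor makes. A cigarette count is supplied by the participant, who knows whether a CO test was done. The intervention is meant to work by making personal risk more vivid, and that could change how consumption is reported as well as how much is smoked. The direction is not known: a participant who was shown a CO figure might under-report, or might report more accurately.

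If reporting shifts in one arm only, the comparison of self-declared counts cannot separate less smoking from different reporting. The article checks cessation biochemically but leaves the reduction aim without any check, although it schedules an objective reading that could supply one at month 12. The stake is a secondary conclusion that cigarette consumption fell when only the answers changed, or a real fall that cannot be supported.

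**Working it through.** **1. The plan's own sample size.** Inputs from Sample size: 5% cessation in controls, a 5-point difference (so 5% against 10%), two-sided alpha 0.05, power 0.80, 10% loss.

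- Arcsine formula: h = 2 × (asin√0.10 − asin√0.05) = 0.1925. Then n = 2 × (2.80 / h)² = 424 per arm, and 424 / 0.90 gives 472. The plan states 471, so the figure reproduces within rounding.
- The pooled formula gives 435, or 484 after loss, which is within 3%.
- Going back from the plan's figure: 471 × 0.90 = 424 followed per arm.

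The sample size is not in dispute. It is used here only to fix the denominators.

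**2. Who contributes to the reduction outcome.** The outcome covers only those who have not quit. Applying the planned cessation rates to those followed:

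- control: 424 × 0.95 ≈ 403
- intervention: 424 × 0.90 ≈ 382

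**3. Effect of a pure reporting shift.** The article gives no SD for the change in cigarettes/day and no size for any reporting difference. I assume SDs of 6, 8 and 10, shifts d of 0.5 and 1 cigarette/day in one arm, and no true effect on consumption.

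SE = SD × √(1/403 + 1/382) = SD × 0.0714

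P(significant) = Φ(d/SE − 1.96) + Φ(−d/SE − 1.96)

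| SD | SE | d = 0 | d = 0.5 | d = 1 |
|---|---|---|---|---|
| 6 | 0.43 | 5% | 21.5% | 64.6% |
| 8 | 0.57 | 5% | 14.1% | 41.7% |
| 10 | 0.71 | 5% | 10.8% | 28.8% |

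**4. What a month-12 CO comparison could detect with 80% power.**

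- All attenders: 2.80 × √(2/424) = 0.19 SD
- Continuing smokers: 2.80 × 0.0714 = 0.20 SD

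The shifts in step 3 run from 0.5/10 = 0.05 SD to 1/6 = 0.17 SD. Even if CO followed consumption perfectly, a true reduction of that size would often be missed.

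**5. Where CO can be used.** Month 6 is a telephone contact, so no reading exists. Baseline CO exists in the intervention group only, so change from baseline cannot be compared. The usable contrast is the month-12 level between randomised arms.

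**The case against.** The strongest reply is that nothing is misstated. The outcome is openly labelled self-declared, a journal article condenses a longer protocol, and a fuller document might give the CO reading a role. That is fair as far as analysis detail goes. But the article lists its outcomes, schedules the reading and does not connect the two, so naming it remains a concrete improvement.

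Several other points stand and limit the concern:

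- That participants know what they received is inferred from the visible test and the personal report. The article does not say what controls are told about the comparison.
- The SDs and shifts are assumed. Nothing in the article shows that a reporting shift exists.
- A comparison of CO in all attenders mixes quitting with cutting down. If more people quit in the intervention arm, mean CO falls even when continuing smokers have not reduced. Restricting to continuing smokers avoids this but conditions on an event after randomisation.
- CO depends on time since the last cigarette. Intervention attaches a timing condition to the baseline test, and Study development does not repeat it for month 12. Intervention participants also know the test, so their behaviour before the visit could differ by arm.

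A reader might infer that the reporting bias is avoidable altogether, or that a reduction should be claimed only when count and CO agree. The documents support neither. Month 6 cannot be checked at all, and step 4 shows that a strict agreement rule would suppress real but small reductions.

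**Conclusion.** The point holds as a cheap improvement. The reduction aim rests only on self-report from participants who can tell whether they had the CO test. An objective reading that the article itself regards as related to consumption is taken in both arms at month 12 and goes unused.

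Under the assumptions in the working, a reporting difference of 0.5 cigarettes/day gives about 11–22% false positives and a difference of 1 gives about 29–65%, against a nominal 5%. These figures show sensitivity. They are not an estimate of bias in this trial.

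A reader might also infer that the trial's main conclusion is exposed. It is not: sustained cessation at 12 months is cotinine-confirmed.

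**What to change.** - Name exhaled CO (ppm) at month 12 as a supportive secondary outcome for the reduction aim.
- Compare it between randomised arms in all attenders, and report it also among continuing smokers so that cessation is not mistaken for reduction.
- Take the reading after the data collection booklet questions are complete, and record time since the last cigarette.
- Report CO beside the self-declared count. Label the month-6 result, and any month-12 reduction that CO does not support, as self-reported only. Do not make agreement a condition for reporting a reduction.

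The cost is one outcome line, one booklet item, a fixed order at the final visit and one analysis in two populations. No new test or visit is needed. The price is a noisy measure with no control-group baseline, nothing to offer at month 6, and limited power for small reductions, so it corroborates the count and does not replace it.
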